### Allocation and follow-up

Patients are followed from baseline (before the start of cancer treatment) and at 4 subsequent follow-ups: 6 months after completion of treatment, and 1, 2, and 3 years after the 6-month follow-up (Fig. 1).

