**Fig. 1 Fig1:**
[figure not shown]
Follow-up and randomisation to the intervention; an oral health care programme. Created in BioRender. [name] (2026) https://BioRender.com/v8xvrby

Standard of care, according to clinical practice in Sweden, is provided to all participants for up to approximately 3 months after treatment. At the 6-month follow-up, patients are randomised (1:1) to receive either the intervention (oral health care programme) or standard of care. A statistician has generated the randomisation list; no members of the research team were involved in this process or have access to the randomisation list. Randomisation is computer-generated using REDCap.

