#### Data collection overview

Clinical/research nurses, dentists and dental hygienists at each site are responsible for the data collection. Data are collected from all participants at baseline, 6 months after the end of treatment (randomisation and start of intervention), and 1, 2 and 3 years after randomisation. Non-adherence and non-retention are registered.

Data gathered through history taking or medical records include, e.g., demographics (sex, age and education), as well as information on diagnosis and treatment (tumour site and stage, treatment modality, comorbidities and medication), work ability and sick leave, eating ability, and habits, including use of nicotine and alcohol, nutritional status (anthropometrics, body composition). Body composition measurements using calf circumference are performed on all participants. Bioelectrical impedance analysis (Bodystat^®^ Multiscan 5000) is used on a subgroup.

In addition, participants complete questionnaires (PROMs) to assess HRQoL, depression, anxiety and stress, health status, self-efficacy, and self-rated oral health (Table 1). The questionnaires are completed digitally or on paper.

**Table 1 Tab1:** Data overview from patient-reported outcome measures, PROMs

Questionnaire	Description
European Organization for Research and Treatment of Cancer Quality of Life Questionnaire-Core 30 (EORTC-C30) [26]	Assesses health-related quality of life in cancer patients. Comprises 30 items covering, e.g., global health status, functional domains (physical, role, emotional, cognitive, and social), symptom scales (fatigue, pain, nausea/vomiting).
EORTC-Head and Neck Cancer Module (EORTC-HN43) [27]	Assesses health-related quality of life in patients with head and neck cancer, an updated version of HN35. Includes 43 items addressing disease- and treatment-specific issues, such as swallowing, speech, senses (taste and smell), pain, social eating, sexuality, and body image, as well as symptoms such as dry mouth and sticky saliva.
Depression Anxiety Stress Scale-21 (DASS-21) [28]	Measures negative emotional states. Consists of 21 items divided into three subscales assessing symptoms of depression, anxiety, and stress.
EQ-5D-3 L [29, 30]	Measures general health status. Consists of five dimensions (mobility, self-care, usual activities, pain/discomfort, and anxiety/depression). Each dimension has three levels of severity.

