### Data processing and analysis

The effects of the intervention will be evaluated in comparison with standard of care. Outcomes will be analysed using either change‑from‑baseline or end‑point values, depending on the nature of each variable. Time‑to‑event outcomes, where applicable, will use time from randomisation to the occurrence of the event of interest.

The main statistical analyses will be performed by statisticians according to the intention-to-treat (ITT) principle. The primary analysis of the EORTC QLQ-HN43 [27] will be conducted using an ANCOVA model adjusting for baseline values, with robust standard errors. Analyses will be performed at each follow-up time point, with the primary comparison at 12 months. To account for within-subject correlation, a linear mixed-effects model with random subject intercepts and a treatment-by-time interaction, using all three follow-up time points, will be used as a sensitivity analysis.

Missing data will be addressed using multiple imputation under the assumption that data are missing at random. Effect size will be estimated using Cohen’s d. Sensitivity analyses to assess the impact of non-compliance will include complete-case and per-protocol analyses. Descriptive statistics will be presented as numbers and percentages for categorical variables, and as means with standard deviation (SD) for continuous variables.

Resource use and societal costs will be used to investigate cost-effectiveness. The economic evaluation will be based on the direct medical costs of specialised healthcare (calculated from diagnosis-related group weights) and drug costs (the register includes costs for dispensed prescription drugs) among HNC survivors, as well as the direct non-medical costs of formal assistance services (assistance and home care, costed using templates from national and municipal statistics), costs for dental care, and indirect costs in the form of productivity loss for sickness absence, estimated according to the human capital approach. A subgroup analysis will be conducted using administrative data on primary care use from one healthcare region and unit costs for such use from national statistics, to identify the effect of including primary care in the evaluation. The economic evaluation will estimate societal costs over a one-year time horizon for each patient; no discounting will therefore be necessary in these analyses. Societal costs will be reported, as well as costs by components and payers.

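### The primary ANCOVA, read with the protocol's own definition of baseline, adjusts for the score before cancer treatment and leaves out the score at randomisation, giving up available precision

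*Protocol article*

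**What the plan says.** All references are to the protocol article.

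- Allocation and follow-up fixes the meaning of baseline: "Patients are followed from baseline (before the start of cancer treatment) and at 4 subsequent follow-ups". The first of those follow-ups is 6 months after treatment ends.
- The text under Fig. 1 places randomisation there: "At the 6-month follow-up, patients are randomised (1:1) to receive either the intervention".
- Data collection overview lists the two visits separately: "Data are collected from all participants at baseline, 6 months after the end of treatment (randomisation and start of intervention". It adds that "participants complete questionnaires (PROMs) to assess HRQoL" and exempts no visit.
- Data processing and analysis states that the primary analysis of the EORTC QLQ-HN43 is "conducted using an ANCOVA model adjusting for baseline values, with robust standard errors", "with the primary comparison at 12 months". No other covariate is named. The mixed model, "using all three follow-up time points, will be used as a sensitivity analysis", has no pre-randomisation score named in it.
- The same section lets outcomes be analysed as change from baseline or as end-point "values, depending on the nature of each variable".

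**The concern.** In most trials baseline and randomisation coincide, so adjusting for baseline means adjusting for the patient's state at randomisation. Here cancer treatment and a further 6 months lie between the two. The Background section says radiotherapy may reduce saliva flow, possibly permanently, and that trismus often progresses for up to 6 months after radiotherapy starts. The sample size rests on a dry-mouth score, which such damage affects directly. The Discussion plans a cohort mixed in site, stage and treatment modality, so patients with similar pre-treatment scores may reach randomisation in quite different states.

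A score taken at randomisation reflects that variation and is closer in time to the 12-month comparison. A score taken before treatment cannot reflect it. At stake is the width of the confidence interval for the primary comparison and, for outcomes analysed as change, extra noise and within-arm changes that are hard to interpret.

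**Working it through.** **Which visit supplies the covariate.** Allocation and follow-up and Data collection overview both separate baseline from the randomisation visit, and Data processing and analysis does not redefine the term. Four follow-ups are listed: 6 months after treatment, then 1, 2 and 3 years later. The mixed model uses three, most naturally the 1-, 2- and 3-year visits. The 6-month score is then neither a covariate nor a response in any stated efficacy model.

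**Inputs.** From Participants: SD 33 (dry mouth at one year, standard of care), difference 10, 125 per arm, two-sided 5%, planned correlation zero. The correlation r between covariate and 12-month score is given for neither visit, so the values of r below are assumptions.

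**The plan's own figure.** The article states about 80% power with these inputs at r = 0. The normal formula gives SE = 33 × √(2/125) = 4.17 and power = Φ(10/4.17 − 1.96) = 66.8%. Simulations of bounded outcomes that kept means of 52 and 42 and an SD of about 33 in both arms gave about 66%. The article does not give its simulated distribution, so its 80% could not be reproduced. That is a separate matter; here the formula serves only to compare one covariate with another.

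**Effect of the covariate.** Residual SD = 33 × √(1 − r²); SE = residual SD × √(2/125); power = Φ(10/SE − 1.96).

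| r | residual SD | SE | power, 125 per arm | total N for 80% |
|---|---|---|---|---|
| 0 | 33.00 | 4.17 | 66.8% | 342 |
| 0.2 | 32.33 | 4.09 | 68.6% | 330 |
| 0.3 | 31.48 | 3.98 | 70.9% | 312 |
| 0.5 | 28.58 | 3.61 | 79.0% | 258 |
| 0.6 | 26.40 | 3.34 | 85.0% | 220 |

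If the pre-treatment score has r of 0.2 to 0.3 and the 6-month score 0.5 to 0.6, the smallest gain is 79.0 − 70.9 = 8.1 points and the largest is 85.0 − 68.6 = 16.4 points.

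**Change from baseline.** With equal variances σ² at both visits (an assumption; the article gives no pre-treatment SD), the variance of the change is 2σ²(1 − r). This exceeds σ², the variance of the end-point value, whenever r < 0.5. It is never below the ANCOVA variance σ²(1 − r²), because the ratio of the two is 2/(1 + r), which is at least 1. The expected between-arm difference is the same in all three analyses, because the pre-treatment value precedes randomisation.

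**The case against.** The strongest reply is that the analysis section may simply mean the randomisation visit. It measures time to event from randomisation and counts three follow-ups where four are listed, as if the 6-month visit were its starting point. That reading is possible, but the only definition of baseline in the article is the pre-treatment one. If the authors meant the other visit, the analysis section conflicts with that definition and needs the same correction.

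Several stronger inferences are tempting, and the document does not support them:

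- A reader might infer bias. There is none: a pre-treatment score precedes randomisation, so adjusting for it is valid. Chance imbalance in state at randomisation is already reflected in the standard error.
- A reader might infer a shortfall against planned power. Planning assumed zero correlation, so it credited nothing to the covariate.
- A reader might take that zero as the authors' admission that the covariate predicts poorly. Participants calls it conservative; it is a planning floor, not evidence.
- A reader might say that change from a pre-treatment value answers the wrong question. The between-arm difference in change estimates the same effect as the difference in end-point values; only its variance differs. Within-arm change is another matter, because it includes treatment effects from before randomisation.
- A reader might say the 6-month score is not used at all. The imputation model is not described and may include it.

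It also stands that the size of the gain is hypothetical, and that the article does not itemise measures by visit, although it exempts no visit from the questionnaires.

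**Conclusion.** The point holds as one of efficiency and definition. On the article's own terms, the primary ANCOVA uses a covariate measured before cancer treatment, and the last score before randomisation has no role in any stated efficacy model. The primary comparison is valid either way. The direction of the gain rests on the article's own account of what treatment does to the mouth. Its size, about 8 to 16 points of power, rests on assumed correlations of 0.2 to 0.3 for the pre-treatment score and 0.5 to 0.6 for the 6-month score, and on SD 33 and 125 analysed per arm. For outcomes analysed as change from the pre-treatment value, the between-arm estimate is likewise unbiased, but it is noisier than the end-point value when r is below 0.5, assuming equal variances. Confidence is high about the definition and low about the exact size.

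**What to change.** State in the analysis section that the covariate in the primary ANCOVA is the score from the 6-month randomisation visit, and enter the same covariate in the mixed model. The pre-treatment score may be added as a second covariate and kept for description. Analyse continuous secondary outcomes by ANCOVA on the follow-up value with the corresponding randomisation-visit value as covariate, in place of the open choice between change and end-point values. Take any reported change scores from the randomisation visit. Use one term for each visit throughout, so that baseline cannot be read two ways.

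The cost is wording in the protocol or the analysis plan. Data collection is already scheduled at that visit, and missing 6-month scores can be handled by the multiple imputation already planned. Recruitment began in September 2025, so the change should be recorded before any outcome data are examined by arm.

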### Participants

Patients diagnosed with HNC are randomly assigned in a 1:1 ratio to either an oral health care programme (intervention) or standard of care. The power analysis was performed based on data from a prospective observational study on HNC (ClinicalTrials.gov NCT03343236) involving individuals with various HNC diagnoses. In that study, we collected data using the European Organisation for Research and Treatment of Cancer Quality of Life Questionnaire – Head and Neck Module (EORTC QLQ-H&N35) [24]. Data from this instrument, specifically the ‘Dry mouth component’ of the EORTC QLQ-H&N35, form the basis for the power calculation, assuming a mean of 52 and a standard deviation (SD) of 33 after one year in the standard of care group.

Sample size was determined using simulation-based power calculations for an ANCOVA model, adjusting for baseline values, with robust standard errors. Simulations enable a skewed outcome bounded between 0 and 100 and a conservative zero correlation between baseline and follow-up. Simulation-based power calculations were chosen due to the discrete and bounded nature of the outcome variable, which violates the assumptions underlying standard normal-theory sample size formulas.

A total of 250 participants (125 per group) provides approximately 80% power to detect a clinically relevant difference of 10 units between groups at a two-sided 5% significance level. To account for potential dropouts, we plan to enrol 300 patients in total that will be randomised. Calculations were performed using R version 4.3.3.

Inclusion started in September 2025. Patients are recruited at different hospitals in Sweden. Clinical/research nurses at each cite identify eligible patients in relation to a multidisciplinary conference, where treatment options for newly diagnosed patients with HNC are discussed and planned. Informed consent is obtained from the participant by the clinical/research nurses. The number of patients who decline participation or who are inadvertently omitted from being approached is documented in the research database Research Electronic Data Capture (REDCap) [25].

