There are important methodological considerations that need to be acknowledged. Given the study design and intervention, blinding will not be feasible. This will pose a particular challenge regarding the PROMs [39]. When an intervention is delivered through direct human interaction, there is an inherent risk that attention bias will affect PROMs. Hence, improvements in PROM scores may not solely reflect the intervention itself but could also result from increased frequency of patient–provider contact. Additionally, patients who are aware of receiving an intervention may report improvements more positively. When using PROMs, there is a risk that patients may adapt to their condition or treatment sequelae, leading to changes in PROM scores that reflect adaption rather than true changes in symptoms. We believe that using PROM instruments will add substantial value and enable us to demonstrate the therapeutic benefit of the oral health care programme from the patient’s perspective. To address the previously described potential biases associated with using PROMs, and to add objectivity, the outcomes measured are not based solely on PROMs but instead on a combination of patient-reported outcomes, clinical indicators, imaging, and biochemical biomarkers.

The extensive data collection is a strength and will enable us to investigate the longitudinal impact of the oral health care programme. To enhance the generalizability of the findings, a diverse and inclusive cohort of patients with HNC, representing different tumour sites, stages, and treatment modalities, will be recruited. We will use REDCap [25] for randomisation, which enables instant and consistent allocation according to a predefined scheme, thereby reducing the risk of human error. The planned feasibility study is an additional strength, as it will enable us to resolve methodological issues early and identify where modifications are necessary to strengthen trial methodology and operational processes [33].

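### The longitudinal sensitivity model has a random intercept as its only covariance term and no robust standard errors, so its visit-specific standard errors are wrong if the spread of the score changes over years 1 to 3

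*Protocol article*

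**What the plan says.** The primary analysis in Data processing and analysis is an ANCOVA on the EORTC QLQ-HN43, adjusted for baseline, with robust standard errors. It is run at each follow-up, and the primary comparison is at 12 months. To allow for correlation within a patient, a sensitivity analysis is added: "a linear mixed-effects model with random subject intercepts and a treatment-by-time interaction, using all three follow-up time points". By Data collection overview, the visits after randomisation are at years 1, 2 and 3. The 6-month visit, at which patients are randomised, is therefore not one of the modelled outcomes. The sentence names no residual structure, random slope, robust standard error or baseline term for this model.

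The only spread given is in Participants: "assuming a mean of 52 and a standard deviation (SD) of 33 after one year in the standard of care group". Nothing is given for years 2 and 3. The Discussion presents the extensive data collection as a strength that "will enable us to investigate the longitudinal impact of the oral health care programme".

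**The concern.** A random intercept with independent residuals is compound symmetry: one variance at all visits and one correlation between any two visits. The score is bounded at 0 and 100 and, by the article's own account, skewed. On such a scale the variance tends to move when the mean moves, and the programme runs for three years with the aim of moving the mean. If the visit variances differ, the model still uses their average at every visit. It then understates the standard error where the spread is large and overstates it where the spread is small.

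Under a steady drift the first and last visits are hit hardest, and the first is the 12-month comparison that this model is meant to check. It is the only described analysis that models all visits jointly. A wrong standard error could make it agree or disagree with the primary result for a purely technical reason.

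**Working it through.** **Inputs from the article.** SD 33 at one year; 125 per arm analysed ("A total of 250 participants (125 per group) provides approximately 80% power to detect a clinically relevant difference of 10 units between groups"); testing "at a two-sided 5% significance level". The article states no variance by visit and no standard error for this model, so there is no planned figure to reproduce. Its power statement rests on the ANCOVA and does not bear on this point.

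**Assumptions.** The SDs at years 2 and 3 (and at year 1 in the rising case), the correlations and the dropout rates below.

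**Step 1, formula.** Take complete data, categorical visit and n per arm. The residual variance estimate is the average visit variance minus the average between-visit covariance, and the intercept variance estimate is that average covariance. Their sum is the average visit variance, so:

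- model SE at every visit = sqrt(2/n × mean of the three visit variances)
- true SE at visit k = sqrt(2/n × variance at visit k)
- type I error at visit k = 2Φ(−1.96 × model SE / true SE)

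The covariance cancels, so a decaying correlation does no harm by itself here.

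**Step 2, numbers at n = 125.**

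- SDs 33/33/33: model SE = 33 × sqrt(2/125) = 4.17, true SE 4.17, type I error 5.0% at each visit.
- SDs 33/31/28: mean variance (1089 + 961 + 784)/3 = 944.67; model SE 3.89; true SEs 4.17/3.92/3.54; ratios 0.931/0.991/1.098; type I error 6.8%/5.2%/3.1%.
- SDs 33/30/26: mean variance (1089 + 900 + 676)/3 = 888.33; model SE 3.77; true SEs 4.17/3.79/3.29; ratios 0.903/0.993/1.146; type I error 7.7%/5.2%/2.5%.
- SDs 28/31/33: the mirror image of the second case, 3.1%/5.2%/6.8%.

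The type I errors depend only on the ratios and so do not change with n.

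**Step 3, simulation with dropout.** Two simulation sets used 300 patients, serial correlation 0.7, about 7-8% loss per year at random given the previous value, and no treatment effect (1,500 and 3,000 runs per setting).

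| Assumed SDs | Year 1, set 1 / set 2 | Year 3, set 1 / set 2 |
|---|---|---|
| 33/31/28 | 6.7% / 7.0% | 4.1% / 3.5% |
| 33/30/26 | 9.0% / 8.0% | 2.7% / 2.5% |
| 28/31/33 | 3.5% / 2.9% | 8.6% / 8.0% |

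With constant SD both sets stay near 5% (4% to 5% in set 2). Direction and size agree with Step 2.

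**Step 4, the randomisation-visit score as a separate matter.** Compared with a model that includes this score, leaving it out multiplies the standard error by 1/sqrt(1 − r²): 1.09, 1.15 and 1.25 for assumed r = 0.4, 0.5 and 0.6. In simulation at constant SD 33 and r = 0.6, including it lowers the SE from about 4.17 to about 3.35.

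**Step 5, adding the score alone does not repair the variances.** Suppose constant SD 33 and serial correlation 0.7, so that the score correlates 0.7, 0.49 and 0.343 with years 1, 2 and 3. The adjusted variances are 1089 × (1 − r²) = 555, 828 and 961, with mean 781. The random-intercept model then gives SE 3.54 at every visit against true values of 2.98/3.64/3.92, and type I error of 2.0%/5.7%/7.7%. Simulation gave 2.1%/5.9%/7.9%.

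**The case against.** The strongest reply is that this is a single sentence in a journal article about a secondary model. It excludes no covariate, residual structure or robust standard error, and an analysis plan that is not shown may settle all three. The harm also needs visit SDs that the article does not give: with constant SD there is no error, and without a score in the model a decaying correlation alone leaves the standard errors right. The ANCOVA with robust standard errors is run at every visit, so inference at years 1, 2 and 3 already has a variance-robust analysis.

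Most of this stands, and it limits the point. It does not remove it. The random intercept is a stated choice, robust standard errors are attached to the ANCOVA only, and a better specification is available at almost no cost.

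A reader might go further in four ways that the article does not support:

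- That the randomisation-visit score is definitely left out. The text is silent; it shows only that the 6-month visit is not a modelled outcome.
- That leaving out that score causes the wrong standard errors. It is a separate matter of precision (Steps 4 and 5).
- That patients with this score but no later visit are lost, and that adding it as a covariate would recover them. A covariate gives such a patient no outcome row, and the article plans multiple imputation without exempting this model.
- That the mixed model is less precise than the primary ANCOVA. The ANCOVA adjusts for baseline, which the article places before cancer treatment, and is not said to use the randomisation-visit score either. The only correlation stated is the planning value, "a conservative zero correlation between baseline and follow-up". The 9%, 15% and 25% compare two versions of the mixed model, not the mixed model with the ANCOVA.

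**Conclusion.** The point holds in a limited form. As written, with independent residuals, the sensitivity model imposes one variance at years 1, 2 and 3, with no stated protection if that is wrong. For modest assumed changes in SD (33 to 28, or 33 to 26), the type I error at the visit with the larger spread is about 7% to 9%, and at the visit with the smaller spread about 2.5% to 4%. A rising SD reverses which visit is affected, and a constant SD leaves it near 5%. These sizes rest on assumed SDs, since the article gives one SD at one visit.

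The primary result and the visit-by-visit ANCOVAs are untouched, so it would be wrong to infer that the trial's three-year conclusions are unsound. This is a minor improvement to a sensitivity analysis.

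**What to change.** Specify the sensitivity model with visit as a categorical factor, treatment by visit, and an unstructured covariance over the three post-randomisation visits. Name a simpler structure with robust standard errors as the fallback if the model does not converge. As a separate gain in precision, include the score from the 6-month randomisation visit and its interaction with visit as covariates; do this together with the covariance change, not in place of it. Report the 12-month contrast from this model next to the primary ANCOVA.

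The cost is about one line in the analysis plan. Three visits need 3 variances + 3 covariances = 6 parameters, which 250 to 300 patients support easily. The 6-month score is already collected, so no new data are needed.
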